**6 WITHDRAWAL**

**6.1 Conditions for Withdrawal**

1. Failure of the subject to attend scheduled visits.
2. Adverse events (including intercurrent illnesses).
3. Occurrence of complications - if Cotrifazid or Lariam, change to standard treatment, if quinine + Fansidar, persist with standard treatment (including other available drugs as considered clinically appropriate)
4. Violations of, and deviations from, the protocol.
5. Subject withdraws consent.
6. Subject lost to follow-up.
7. Administrative/other.

***Subjects may withdraw from the trial at any time and for any reason, without affecting their right to treatment by the investigator****.* The investigator has the right to withdraw a subject for any reason which is in the best interests of the subject, including intercurrent illness, adverse events, or treatment failure.

Although withdrawals should be avoided if at all possible, it is understood that withdrawals may occur during a trial. Whenever a subject is withdrawn from a trial, FOR WHATEVER REASON, a final trial evaluation must be completed for that subject, stating the reason for withdrawal. All documentation concerning the subject must be as complete as possible.

Withdrawals due to non-attendance must be followed up by the investigator to obtain the reason for non-attendance.

WITHDRAWALS DUE TO INTERCURRENT ILLNESS OR ADVERSE EVENTS MUST BE FULLY DOCUMENTED IN THE CASE RECORD FORM, WITH SUPPLEMENTARY INFORMATION WHERE AVAILABLE AND/OR APPROPRIATE.

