**5.3 Assessment of Efficacy**

**5.3.1 Primary Efficacy Parameters**

The primary parameters of efficacy i) fever clearance time, ii) parasite clearance time, iii) failure rate, iv) occurrence of complications, information collected from day 1,2,3, 7 and 14.

Thick and thin blood films will be Giemsa stained and species-specific density will be counted per/200 white blood cells (WBC). Slides will be declared negative if no parasites are seen in 100 thick film fields. Parasite density per microliter blood will be calculated by multiplying the parasitemia/200 WBC by a WBC count of 10000/L in children aged < 5 years and of 8000/L in persons aged > 5 years.

1. **Secondary Efficacy Parameters**

The secondary parameters of efficacy are i) symptom clearance time, information collected at day 1,2,3, 7 and 14, and ii) haemoglobin concentration from samples collected at day 14.

1. **Assessment of Pharmacology**

Pharmacokinetics will be assessed in a small subsample of patients (5). Blood will be drawn (2 ml by venepuncture) at hour 2, 8, 16, 24, 36, 72.

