**9 SUBJECT ANALYSIS POPULATIONS**

All subjects who are randomised to receive either Cotrifazid or the comparators constitute the ‘*intention to treat population’*.

Subjects will be excluded from analysis of *safety* if they do not receive at least one daily dose of Cotrifazid or comparators, and one follow-up visit. Remaining subjects constitute the ‘*safety population’.*

Subjects will be excluded from final analysis of *efficacy* if they do not receive the full dose of Cotrifazid, or the full dose of Fansidar + at least 3 daily dose of quinine, and one follow-up visit. Remaining subjects constitute the ‘*efficacy population’*.

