**10.2 Study Design**

This is a multicentric, open, block-randomised, comparative study.

1. **Sample Size Calculation**

The overall sample size of 330 (110 in Cotrifazid group, 110 in Lariam group and 110 in standard treatment group) is sufficient to demonstrate that Cotrifazid is not inferior to Lariam or quinine and Fansidar, assuming a rate of treatment success of 95% with Lariam or quinine and Fansidar and a clinically acceptable rate of treatment success of 86% or more in the Cotrifazid group, a 10% loss of follow-up (80% power, 95% confidence limits, one-sided test) (formula from Jones et al, 1996).

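### Section 6.1 does not separate stopping study drug from leaving the trial, and section 9 admits patients to the efficacy population without a day-14 outcome while excluding Cotrifazid patients who fail and are switched early

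*Protocol*

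**What the plan says.** **Withdrawal (section 6.1).** The listed conditions include adverse events, complications and "Violations of, and deviations from, the protocol". The investigator may also withdraw a subject for reasons "including intercurrent illness, adverse events, or treatment failure". What follows is stated once, for all reasons: "Whenever a subject is withdrawn from a trial, FOR WHATEVER REASON, a final trial evaluation must be completed for that subject". The section does not say whether the remaining visits continue. The entry on complications mixes the two ideas: it describes a change of treatment in two arms and continuation of treatment in the third, yet lists all of them as withdrawal.

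**Follow-up (sections 5.2.1, 5.2.4, 5.3.1).** Section 5.2.1 has all subjects seen on days 7 and 14 to pick up late adverse events or clinical failure. Section 5.2.4 follows reported adverse events until they are resolved or explained. Section 5.3.1 bases the primary efficacy parameters, including failure rate and complications, on "information collected from day 1,2,3, 7 and 14". The synopsis counts both early and late treatment failure.

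**Efficacy population (section 9).** A patient needs the full Cotrifazid dose, or full Fansidar and "at least 3 daily dose of quinine, and one follow-up visit". No day-14 assessment is required, and no dosing rule is given for Lariam.

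**Scoring.** Neither section 9 nor section 10.4.1.1 says how a patient without a day-14 outcome is classified.

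**The concern.** The events that end participation are either primary outcomes themselves or closely tied to how the patient is doing. If withdrawal ends the visits, day-14 outcomes go missing for reasons related to outcome. The trial is open (section 4.2), so these decisions are made with the arm known.

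Section 9 then adds two weaknesses. It lets in patients whose follow-up stopped before late failure could be seen. It also removes patients who failed early if the failure led to a change of drug before the Cotrifazid course was complete. In a non-inferiority comparison, anything that hides failures can make a worse drug look acceptable. An analysis plan can choose how to treat a missing day-14 result, but it cannot recover a blood film that was never taken.

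**Working it through.** **Inputs.** The sample size paragraph in section 10 assumes 95% success in each comparator arm. For the test drug it takes "a clinically acceptable rate of treatment success of 86% or more in the Cotrifazid group". The implied margin is 95 − 86 = 9 points, or failure of 14% v 5% at the margin. It also gives 110 per arm, 10% loss, 80% power and a one-sided test. I take one-sided 5% from section 10.4.1.1.

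**The plan's own figure.** With p = 0.95 and margin 0.09, n = 2p(1−p)(z₀.₉₅ + z₀.₉₀)²/margin² = 0.095 × (1.6449 + 1.2816)²/0.0081 = 0.095 × 8.564/0.0081 = 100.4. Then 100.4 × 1.1 = 110.5, which matches 110. The plain one-sided 5% non-inferiority formula needs 73 (82 after dividing by 0.9). The sample size is not the problem here.

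**The passages side by side, for three patients.**
- *Any arm, withdrawn on day 4 for an adverse event.* Section 6.1 gives a final evaluation on leaving. Section 5.2.1 still expects days 7 and 14. A site cannot tell which governs.
- *Quinine + Fansidar, three quinine days, last seen on day 3.* Dosing and visit conditions are both met, so the patient is in the efficacy population. Failure after day 3 is unobserved.
- *Cotrifazid, rising parasitaemia, switched before day 7 (section 2.1).* The full dose was not received, so the patient is out of the efficacy population and the failure goes with them. A quinine patient doing badly has no other study regimen to be switched to and needs only 3 of 5 quinine days, so the failure usually stays in. Lariam is given over 24 hours (section 5.1.1.3) and has no dosing rule.

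**Size of the first gap (assumption: missing outcomes left as non-failures).** With 10% loss at random in both arms:
- Cotrifazid failure: 0.14 × 0.9 = 12.6%
- Comparator failure: 0.05 × 0.9 = 4.5%
- Difference: 8.1 points instead of 9.0

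The difference shrinks because Cotrifazid has more failures to lose (1.4 points v 0.5). If loss fell only on the comparator, the effect would run the other way.

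The chance of wrongly declaring non-inferiority is Φ[(0.09 − d)/SE − 1.645], where d is the observed difference and SE = √{[p₁(1−p₁) + p₂(1−p₂)]/110}. For d = 0.081, SE = 0.0373 and the chance is about 8% against a nominal 5%.

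Range, assuming that the missing 10% fail at 2 or 3 times their arm's average:
- 2 times: 14 − 2.8 = 11.2% v 5 − 1.0 = 4.0%, difference 7.2 points, chance about 13%
- 3 times: 14 − 4.2 = 9.8% v 5 − 1.5 = 3.5%, difference 6.3 points, chance about 20%

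**Size of the second gap.** If a share e of the Cotrifazid arm fails early and is excluded, observed failure is (0.14 − e)/(1 − e), which is below 0.14 for any e > 0. For each single percentage point, (0.14 − 0.01)/0.99 = 13.1%, about 0.9 points lower, if the comparator is unaffected. The protocol gives no basis for the size of e, so only the direction and this unit rate can be stated.

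**The case against.** **Scoring is an analysis-plan matter.** No passage scores missing outcomes as non-failures, and the 10% inflation fits lost patients leaving the denominator. This stands. A reader might infer from section 9 that patients without a day-14 result count as successes, but section 9 defines membership, not scoring. Dropping lost patients helps only if the loss is unrelated to outcome: 12.6/90 − 4.5/90 = 14.0% − 5.0% = 9.0 points. If the missing patients fail at 2 to 3 times the average, the complete-case difference is 11.2/90 − 4.0/90 = 8.0 points, or 9.8/90 − 3.5/90 = 7.0 points. Outcome-related loss therefore still matters.

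**One visit is not enough for entry.** Correct: the dosing condition also applies. A Cotrifazid patient stopped before 7 days is excluded from the efficacy population, not counted there as a success. That removes one bias and creates another.

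**Withdrawal does not end all observation.** A reader might infer that the late failures and late adverse events of withdrawn patients can never be seen. The protocol does not support this. Section 5.2.1 keeps the visits for all subjects, section 5.2.4 follows adverse events already reported, and section 2.1 describes changing treatment without calling it withdrawal. What remains is a conflict between sections.

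**Complications and failures that trigger withdrawal are already recorded.** True, and withdrawal for failure is discretionary. The gap concerns what happens after withdrawal for other reasons, and early failures that section 9 removes.

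**The intention-to-treat population keeps everyone.** It does, so the exclusion of early failures would show there. It inherits any day-14 outcomes lost through section 6.1, and section 9 ties the final efficacy analysis to the efficacy population.

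**Conclusion.** The concern holds in this form: sections 6.1 and 5.2.1 conflict on whether patients who stop or change study drug are still assessed on days 7 and 14. Section 9 also admits patients with no day-14 outcome and excludes Cotrifazid patients who fail and are switched before 7 days.

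The first gap is modest under random loss: 9.0 points becomes 8.1 at the plan's own 10%, assuming that missing outcomes are left as non-failures. It is larger if loss is related to failure, and its direction depends on which arms lose patients. The second favours Cotrifazid as long as early exclusions are more frequent there, as the 7-day and 3-day rules suggest; its size is unknown. The protocol does not establish that a false claim will follow, only that these rules leave room for one. It should be corrected in the protocol because it concerns which data are collected.

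**What to change.** - **Section 6.1:** distinguish stopping or changing study drug from leaving the trial, and reconcile with section 5.2.1. State that every randomised patient who has not withdrawn consent keeps the scheduled day 7 and day 14 assessments, whatever treatment is then being given.
- **Section 9:** replace the single-visit requirement with a known day-14 outcome or an earlier treatment failure. Keep patients who failed before completing the course in the efficacy population, as failures.
- **Missing outcomes that remain:** counting them as failures is at most a sensitivity analysis. Under 10% random loss it gives 22.6% v 14.5%, again 8.1 points, so it does not correct the shrinkage.

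The cost is protocol wording and some tracing of patients who stopped study drug. The visits are already scheduled.

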**6.2 Replacement Policy**

Recruitment of replacement subjects is unnecessary.

**7 ETHICS**

The responsibility for conducting clinical trials to the highest possible standards lies with the sponsor, monitor, and investigator.

**7.1 Declaration of Helsinki and Good Clinical Practice**

The investigator will ensure that this trial is conducted in full conformance with the principles of the *Declaration of Helsinki* (as amended in Tokyo, Venice and Hong Kong).

Furthermore, it is the responsibility of the investigator to ensure that the trial is performed in accordance with Good Clinical Practice (cf Klinische Arzneimittelprüfungen in der EU), and with all local laws and regulations concerning clinical trials.

This protocol complies with the Department of Health and Human Services (HHS) regulations for the protection of Human Research Subjects (45 CRF 46).

**7.2 Informed Consent**

The investigator will obtain verbal informed consent from each subject participating in the trial or from his/her parents or guardians, after explanation of the aims, methods, benefits and potential hazards of the trial (written informed consent is inappropriate in this setting where few parents are able to write). The consent will be obtained in front of a witness and BEFORE any trial-specific procedures will be performed on the subject.

It will be made completely and unambiguously clear to each subject that they are free to refuse to participate in the trial, or to withdraw their consent at any time and for any reason, without incurring any penalty or withholding of treatment on the part of the investigator.

**7.3 Ethics Committee Approval**

It is the responsibility of the investigator(s) to submit a copy of this protocol and consent form to the Medical Research Advisory Committee of Papua New Guinea in order to obtain INDEPENDENT approval to conduct the trial. Approval from the committee must be obtained before starting the study, and should be documented in a letter to the investigator specifying the date on which the committee met and granted the approval

**7.4 Confidentiality and Data Protection**

The investigator must ensure that the subject's anonymity will be maintained. Subjects will be identified on the case report forms by their ID. The investigator will keep a separate confidential enrolment log which matches identifying codes with the subjects' names and residencies.

**8 ADMINISTRATIVE PROCEDURES**

**8.1 Drug Supply**

Fatol Arzneitmittel GmbH will supply the investigator with the drug and sufficient support to conduct the trial according to the agreed protocol.

**8.2 Monitoring**

Fatol Arzneitmittel GmbH will provide a trained “Trial Monitor” to assist the investigator in conducting the trial. This monitor will have the responsibility of reviewing the ongoing trial with the investigator to verify adherence to the protocol and to deal with any problems if and when they arise. At all times the monitor will maintain the confidentiality of trial documents.

**8.3 Sponsor’s Responsibilities**

A special insurance will be contracted to (i) provide treatment and/or compensation in the event of an injury to or the death of a subject, as a result of his/her participation in this clinical trial, and (ii) insure the investigator(s) against or indemnify them for losses resulting from liability for such injuries or deaths.

**8.4 Investigator's Responsibilities**

The investigator agrees to conduct the trial in accordance with the procedures and requirements laid out in this protocol. In particular, the investigator agrees to conduct the trial in accordance with Good Clinical Practice and strict ethical principles (see section 7). Any modification to the agreed protocol must be approved, if appropriate, by the ethics committee approving the original protocol, BEFORE any modifications are put into effect.

It is the responsibility of the investigator to complete and sign a case report form for each subject in the trial.

Each case report form must be completed legibly. Erroneous values and/or text must not be obliterated (for example, covered with correction fluid). Instead, the error should be crossed out with a single line, the correct value/text added, and the correction signed and dated by the investigator.

In the event of an expected or unexpected serious adverse event (IRAE), the investigator is to notify the clinical monitors within one working day. IRAEs are to be reported, whether or not they are considered related to the treatment.

In addition to the case report form, the investigator will maintain adequate records that fully document the progress of the trial. Copies of these trial records and related documents must be kept on file by the investigator for a period of no less than five years. ALL DOCUMENTATION AND MATERIAL FOR THIS TRIAL (CASE REPORT FORMS, PROTOCOL, ETC.) ARE TO BE RETAINED IN A SECURE PLACE AND TREATED AS CONFIDENTIAL MATERIAL.

The investigator agrees to allow the monitors to access to any or all of the trial materials needed for source data verification and proper review of trial progress. The investigator (or deputy) agrees to assist the monitor in resolving any problems that may be detected during or after the study period.

The investigator agrees to comply with regulatory authority requirements regarding the auditing of this trial.

The investigator has the right to request premature termination of the trial for administrative or other reasons. Should this be necessary and agreed upon, the necessary procedures will be arranged after review and consultation by all parties to ensure protection of the subjects' interests.

By signing this document the investigator indicates that he/she has read and fully understood the protocol, and agrees to abide by all the requirements of the protocol.

**8.5 Publications**

One of the goals of a clinical trial, in addition to demonstrating safety and efficacy, is to provide publications.

For this study all papers should be authored by representatives of PNGIMR and STI.

**9 SUBJECT ANALYSIS POPULATIONS**

All subjects who are randomised to receive either Cotrifazid or the comparators constitute the ‘*intention to treat population’*.

Subjects will be excluded from analysis of *safety* if they do not receive at least one daily dose of Cotrifazid or comparators, and one follow-up visit. Remaining subjects constitute the ‘*safety population’.*

Subjects will be excluded from final analysis of *efficacy* if they do not receive the full dose of Cotrifazid, or the full dose of Fansidar + at least 3 daily dose of quinine, and one follow-up visit. Remaining subjects constitute the ‘*efficacy population’*.

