**5** **STUDY PROCEDURES**

**5.1 Drug**

**5.1.1 Drug Administration**

**5.1.1.1 Dosage Regimen & Rationale for Selection**

The treatment dosage and schedule for Cotrifazid will be the following : subjects > 40 kg 2 x 2 tablets, subjects < 40 kg and > 20kg  2 x 1 tablet, subjects < 20 kg  2 x ½ tablet, every 12 hours.

The treatment dosage and schedule for Lariam will be the following : subjects > 60 kg : 6 tabs (3 at hour 0, 2 at hour 8, 1 at hour 24), subjects > 40 kg and < 60 kg : 5 tabs (2, 2, 1), subjects < 40 kg and > 30 kg : 3 ½ tabs (1 ½ , 1, 1), subjects < 30 and > 20 kg : 3 tabs (1, 1, 1), subjects < 20 kg and > 10 kg : 1 ½ tabs ( ½ , ½, ½ ), subjects < 10 kg : ¾ tablet ( ¼ , ¼, ¼ ).

The treatment dosage and schedule for quinine will be the following : subjects > 60 kg  3 x 600 mg quinine /day, subjects < 60 kg  3 x 10 mg/kg/day every 8 hours.

The treatment dosage and schedule for Fansidar will be the following : subjects > 40 kg  3 tablets, subjects < 40 kg and > 30 kg 2 tablets, subjects < 30 and > 20 kg 1 ½ tablet, subjects < 20 kg and > 10 kg 1 tablet, subjects < 10 kg ½ tablet.

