## 5.2.2 Adverse Events

An adverse event is **ANY** type of adverse change from the trial subject's pre-drug baseline condition. **ALL** adverse events MUST be reported by the investigator without 'filtration', whether considered treatment-related or not. The wording used in English will be drawn from a list of preferred terms, with their closest equivalent in pidgin.

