**10 STATISTICAL STATEMENT**

**10.1 Statistical Hypothesis**

Study hypotheses:

i) Cure rate of resistant malaria after Cotrifazid treatment is not inferior to the one obtained after treatment with mefloquine or quinine and Fansidar.

ii) Cotrifazid is safe to use in semi-immune patients with resistant malaria. No IRAE attributable to the drug is expected in the subjects.

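### The safety population requires a daily dose and a follow-up visit, so some treated patients with early events can be left out of the adverse-event comparison

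*Protocol*

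**What the plan says.** Section 9 of the protocol defines three populations. The intention-to-treat population has no condition beyond randomisation; its definition begins "All subjects who are randomised to receive either Cotrifazid or the comparators constitute the". The safety population is narrower, since patients are left out of it "if they do not receive at least one daily dose of Cotrifazid or comparators, and one follow-up visit". The efficacy sentence that follows has the same construction; for the standard-treatment arm it asks for "the full dose of Fansidar + at least 3 daily dose of quinine, and one follow-up visit".

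Section 5.1.1.1 gives the schedules. Cotrifazid is taken twice a day (for the lightest patients, "subjects < 20 kg 2 x ½ tablet, every 12 hours") and quinine three times a day (below 60 kg, "subjects < 60 kg 3 x 10 mg/kg/day every 8 hours"). Lariam is taken at hours 0, 8 and 24. Section 2.1 puts the first scheduled follow-up at hour 24.

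On adverse events, Section 5.2.2 counts any adverse change once chemotherapy has begun, with no minimum dose, and requires that all "adverse events MUST be reported by the investigator without 'filtration', whether considered treatment-related or not". Section 10.4.2 compares adverse-event rates between Cotrifazid and the comparators. Section 10.1 adds, as part of the safety hypothesis: "No IRAE attributable to the drug is expected in the subjects".

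**The concern.** A safety population should not be selected on the outcomes it is meant to measure. Whether a patient completes a day's doses, and whether the patient is still there to be seen, are both settled after the first intake, and early intolerance, deterioration or death can prevent either.

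The protocol foresees such cases. Section 2.1 allows a change to standard treatment for tolerance problems, and Section 6.1 lists adverse events and complications among the grounds for withdrawal. Section 1.2 makes safety a primary parameter. What is at stake is therefore the completeness of a primary comparison at its earliest time points: an event could be in the case report form and in the report to the monitors, yet be absent from the numerator and denominator in Section 10.4.2.

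**Working it through.** The protocol states no figure that depends on this definition, so there is none to reproduce. The check is a reading of the sections together, followed by an illustration.

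**1. What a daily dose means.** The efficacy sentence counts quinine in daily doses, and quinine is given every 8 hours, so a daily dose is a day's supply and not one intake. On the Section 5.1.1.1 schedules:

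| Drug | Intakes within the first 24 hours | Last of these |
|---|---|---|
| Cotrifazid | hours 0, 12 | hour 12 |
| Quinine | hours 0, 8, 16 | hour 16 |
| Lariam | hours 0, 8, then 24 | a daily dose is not defined |

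A patient on Cotrifazid or quinine who takes only the first intake has not had a daily dose of that drug.

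**2. How the two conditions combine.** The sentence can be read in two ways.

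- *Both are required, so missing either one excludes.* This is the natural reading and matches the efficacy sentence. It excludes a patient who stops part-way through day 1, and also one who completes day 1 but has no follow-up visit.
- *Exclusion only if both are missing.* Fewer patients go, but one who took part of day 1 and then died or left before any visit is still excluded.

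Some treated patients are lost under either reading.

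**3. Is the patient restored elsewhere?** No. Section 10.4.2 names no population, so the safety population of Section 9 is the one that applies, and no other section adds treated patients back.

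**4. Illustration.** The number k of treated patients with an early event who are excluded is an assumption, since the protocol gives no rate. The arm size of 110 comes from the sample size section. Assume no other events in the arm. Counting everyone treated gives k/110; applying the rule gives 0/(110 − k). Intervals are exact (Clopper-Pearson) two-sided 95% limits; for zero events in n the upper limit is 1 − 0.025^(1/n).

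| k (assumed) | Everyone treated | After exclusion |
|---|---|---|
| 1 | 1/110 = 0.9% (0.02% to 5.0%) | 0/109, upper limit 3.3% |
| 3 | 3/110 = 2.7% (0.6% to 7.8%) | 0/107, upper limit 3.4% |
| 5 | 5/110 = 4.5% (1.5% to 10.3%) | 0/105, upper limit 3.5% |

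For example, 1 − 0.025^(1/107) = 0.034. In each row the point estimate falls to zero and the upper limit falls as well, although k events occurred.

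**The case against.** The strongest reply is that few patients would be lost, because other provisions may keep them in. Section 2.1 allows more intensive assessment than the scheduled visits, Section 5.2.1 has patients followed clinically every day for the first four days, Section 5.1.1.4 has a nurse supervise dosing for the first three days, and Section 6.1 requires a final evaluation for every withdrawal. Section 9 does not say that the visit must be the one at hour 24. A patient switched to standard treatment on day 1 might be said to have received a daily dose of a comparator. All of this is fair. The text leaves open whether an unscheduled contact or a switch satisfies the conditions, so exclusion is possible and not certain for many of these patients. It does not rescue a patient who took part of day 1 and had no further contact.

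Four stronger readings are tempting, and the protocol does not support them.

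- *Everyone who reacts to the first dose is removed.* A patient who reacts, completes the day's doses and is seen at hour 24 stays in.
- *Section 9 contradicts the unfiltered reporting rule.* Section 5.2.2 governs what investigators report; Section 9 governs who is analysed. Early events still reach the case report form, and serious ones reach the monitors within one working day under Section 5.2.3. The two sit awkwardly together but do not conflict.
- *The rule favours one arm.* The number of intakes in a daily dose differs, but the hour-24 visit is common to all arms and falls after the last first-day intake of both Cotrifazid and quinine. Neither the direction nor the size of any imbalance can be derived.
- *One excluded patient reverses the safety conclusion.* Section 10.1 states an expectation, with no test or decision rule tied to the safety population. An early reaction is also not necessarily an immediately reportable event; Section 5.2.3 itself makes this point about prolonged vomiting.

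**Conclusion.** The point holds in a limited form. Section 9 makes entry to the safety analysis depend on tolerance and survival after treatment begins, and can omit some treated patients from the adverse-event comparison. The protocol fixes this definition itself, so it is not a detail left to an analysis plan.

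The effect cannot be sized from the protocol. The shifts from 0.9% or 2.7% to zero show what one or three exclusions would do in an arm of 110. They assume that each such patient has an event, that each is in fact excluded, and that the arm has no other event. The conclusion also rests on reading a daily dose as a day's supply and on Section 10.4.2 using the safety population. It extends neither to the collection and expedited reporting of events, which are sound on this point, nor to any claim of bias towards a particular arm.

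**What to change.** Replace the safety sentence in Section 9 with a definition along these lines: the safety population comprises all randomised subjects who took any amount of study drug; no follow-up visit is required; subjects are analysed by the first study drug they actually received; events that begin after a switch to standard treatment are included and flagged. State in Section 10.4.2 that the adverse-event comparison uses this population. Naming the first drug received matters because Sections 2.1 and 6.1 allow patients to change treatment, which would otherwise leave their group unclear.

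The cost is a short rewording. No new data are needed: early dosing is supervised, all adverse events are already recorded, and withdrawals already require a final evaluation. The sample size does not change, since it rests on treatment success rates. The price is that observed event rates may be slightly higher and a few subjects will contribute only short follow-up, which the report should state.
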